### Sample Size

The primary objective of this trial was to evaluate the therapeutic efficacy of zishenyizhi pill in patients with CSVD-related cognitive impairment. The sample size was estimated based on an anticipated superiority in the MoCA score among the intervention group compared to the control group. On the basis of previous pilot data and clinical judgment, we assumed a mean difference (δ) in MoCA score change of 0.5 between the 2 groups, with a common SD (σ) of 1.52. A 2–independent-sample *t* test was used for the calculation. With a significance level (α; 2-sided) set at .05, a desired power (1 – β) of 90% for detecting this difference, and an allocation ratio (*K*) of 1:1, the required sample size per group was calculated using the following formula for a superiority trial: 
[figure not shown]

. As a result, 98 participants were needed in the experimental and control groups. Accounting for a 20% anticipated dropout rate, we planned to enroll 123 participants per group, totaling 246.

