### Limitations

Nevertheless, this study is subject to several methodological limitations. The nonrandomized observational design carries an inherent risk of selection bias and confounding. Despite stratification based on zishenyizhi pill use, baseline differences in patient characteristics—such as disease severity, comorbidities, and socioeconomic status—may persist between the intervention and control groups, potentially influencing outcome interpretation. The absence of randomization compromises internal validity as unmeasured confounders, including genetic predispositions and lifestyle factors, could independently affect cognitive trajectories.

Although real-world studies prioritize external validity, the limited control over confounding variables constrains the ability to establish causal inferences regarding the therapeutic efficacy of zishenyizhi. In addition, the sample size, while feasible for this preliminary investigation, was not derived from a formal superiority test calculation and was based on a conservative effect size estimate. Consequently, this study may be underpowered to detect differences smaller than 0.5 points on the MoCA, which could represent clinically meaningful but more modest treatment effects, particularly for secondary outcomes. This also limits the potential for meaningful subgroup analyses to explore personalized treatment responses.

Furthermore, the reliance on neuropsychological scales as primary end points without incorporating neuroimaging biomarkers such as magnetic resonance imaging–based quantification of white matter hyperintensity volume or microbleed burden restricts mechanistic interpretation. Objective biomarkers are essential to determine whether cognitive improvements correspond to structural or molecular changes in CSVD pathology. Finally, the 12-week observation period may be insufficient to evaluate the long-term efficacy, safety, and sustained cognitive benefits of zishenyizhi given the chronic and progressive nature of CSVD. Short-term assessment could miss delayed treatment effects, disease progression patterns, or late-emerging adverse events, which are critical in the context of vascular cognitive disorders.

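### The stated inputs need about 195 evaluable participants per group, not 98; on the stated t test, power for 0.5 MoCA points is about 63% to 73%, not 90%

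*Protocol article*

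**What the plan says.** Under Sample Size, the protocol article presents a calculation for superiority on the MoCA. It gives the effect and spread: "we assumed a mean difference (δ) in MoCA score change of 0.5 between the 2 groups, with a common SD (σ) of 1.52". It names the two-independent-sample t test as the basis, with alpha "2-sided) set at .05", power "of 90% for detecting this difference" and equal allocation. The formula, which is an image and is not shown, is described as giving the number per group. The result is "As a result, 98 participants were needed in the experimental and control groups". A 20% dropout allowance takes this to 123 per group and 246 in total.

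Under Statistical Analysis, the primary comparison is an analysis of covariance (ANCOVA) of MoCA change adjusted for baseline MoCA, under the intention-to-treat principle.

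Under Limitations, the article says that the sample size "was not derived from a formal superiority test calculation and was based on a conservative effect size estimate", and that "this study may be underpowered to detect differences smaller than 0.5 points on the MoCA".

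**The concern.** Every input of a standard two-group calculation is printed, and so is the result, but the result does not follow from the inputs. The stated number is about half of what they require.

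This matters for reading the primary comparison. If the result is not significant, a reader who trusts the Sample Size section will take it as a negative finding from a study with 90% power for 0.5 points. On the stated test, the chance of missing a true 0.5-point difference is about 37% with 98 evaluable per group and about 27% with 123, not 10%.

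The Limitations section does not repair this. It disowns the calculation that the Sample Size section presents, and its caution about power starts below 0.5 points, although the shortfall is already present at 0.5.

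**Working it through.** **Inputs (all from Sample Size):** difference δ = 0.5; SD σ = 1.52; two-sided alpha .05, so z = 1.960; power 90%, so z = 1.2816; allocation 1:1; 98 evaluable and 123 enrolled per group.

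**1. Trying to reproduce 98.**

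- Two-sample formula: n per group = 2(z₁ + z₂)²σ²/δ² = 2 × (1.960 + 1.2816)² × 1.52²/0.5² = 2 × 10.507 × 2.3104/0.25 = 194.2, so 195. The exact t test gives 195.2, so 196.
- The same formula without the factor 2: 10.507 × 2.3104/0.25 = 97.1, which rounds up to 98.
- Other two-sample variants do not give 98: one-sided .05 at 90% gives 158.3 (159); two-sided at 80% gives 145.1 (146); one-sided at 80% gives 114.3 (115).
- The dropout step does reproduce: 98/0.80 = 122.5, so 123.

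**2. Could 98 be a total for both groups?** No. The text says the formula gives the size per group, and 98/0.80 leads to the 123 that is stated per group.

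**3. Power at 0.5 points on the stated t test.** The standard error of the difference is σ√(2/n).

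| Evaluable per group | Standard error | 0.5/SE | Power, normal | Power, exact t |
|---|---|---|---|---|
| 98 | 0.217 | 2.303 | 63.4% | 63.0% |
| 123 | 0.194 | 2.580 | 73.2% | 72.9% |
| 196 | 0.154 | 3.257 | – | 90.1% |

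**4. Difference detectable with 90% power.** By normal approximation this is (1.960 + 1.2816) × SE:

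- 98 per group: 3.2416 × 0.217 = 0.70 (exact t: 0.71).
- 123 per group: 3.2416 × 0.194 = 0.63 (exact t: 0.63).

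**5. What the ANCOVA could add.** The article gives no correlation r between baseline and week 12, so the r values here are assumptions. The answer also depends on which SD 1.52 is. For 98 per group, with equal variances at both visits:

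- If 1.52 is the SD of change, the residual variance is 1.52²(1 + r)/2. Power is 75% at r = 0.5, 70% at r = 0.7 and 68% at r = 0.8.
- If 1.52 is the SD of the score itself, the residual variance is 1.52²(1 − r²). Power is 75% at r = 0.5, 89% at r = 0.7 and 97% at r = 0.8.

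Unequal variances widen the range again. With 1.52 as the SD of change and r from 0.5 to 0.8, a week-12 SD of 0.7 to 0.8 times the baseline SD gives about 82% to 92%, and 1.2 times gives about 63% to 69%.

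**6. The two sections side by side.** Sample Size reports a superiority formula with alpha, power, difference and SD. Limitations says the size did not come from a formal superiority calculation. Both cannot stand. Limitations also warns of low power below 0.5 points, whereas step 3 shows 63% to 73% at 0.5 itself.

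**The case against.** The strongest reply is the ANCOVA. The primary analysis is not the t test used for sizing, and adjustment for baseline can reduce the residual variance. This stands in part: under some of the assumptions in step 5, power with 98 per group reaches 90% or more. A reader might infer that the ANCOVA cannot rescue the design. The documents do not support that, because it needs 1.52 to be the SD of change and the variances to be equal at both visits. Change is the likelier reading, since the difference is in change, but the SD is not labelled. Equally, the documents do not support relying on the gain: no correlation is stated, and the calculation is explicitly a t test.

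A second reply is that an intention-to-treat analysis could include all 123 per group. This also stands, and it is why the power is given as a range. It lifts the figure to about 73%, still short of 90%.

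Third, the omitted factor 2 is an inference from the arithmetic, because the formula is not shown. The match is close, but the mismatch between inputs and result does not depend on that explanation.

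Fourth, the Limitations section says the study may be underpowered below 0.5 points; it does not say that power is adequate at 0.5. That is fair. The objection to the sentence is that its threshold is too low, not that it makes an explicit false claim.

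A reader might also infer that the disclaimer about a formal calculation is the wrong statement and should be deleted. The documents do not settle which section is right. Since 98 does not follow from the stated method, the disclaimer may be the accurate one.

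**Conclusion.** The point holds. The printed inputs require about 195 evaluable participants per group (196 by exact t test), and 98 is about half of that. On the stated t test, power for 0.5 points is about 63% with 98 evaluable per group and about 73% with all 123, so 90% is not met in either case. The difference detectable with 90% power is about 0.71 points with 98 per group and 0.63 with 123.

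These figures rest only on the article's own difference, SD, alpha and allocation, and on the t test it names. They are before any gain from baseline adjustment, whose size is unknown and was not used in the sizing. It would therefore go too far to say that the real power of the primary ANCOVA is 63%.

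The Sample Size and Limitations sections contradict each other on the origin of the number, and the 0.5-point threshold in Limitations is too low.

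**What to change.** Keep 246 and correct the statements:

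1. **Sample Size:** replace the 90% claim. State that, by two-sample t test with SD 1.52 and two-sided alpha .05, power for a 0.5-point difference is about 63% with 98 evaluable per group and about 73% with 123, and that 98 per group give 90% power for about 0.71 points.
2. **Sample Size and Limitations:** reconcile whether a formal superiority calculation was made, so that one account appears in both places.
3. **Limitations:** change the threshold from 0.5 to about 0.7 points, and add that a non-significant result does not by itself exclude a 0.5-point benefit.
4. **If an ANCOVA gain is to be claimed:** state the assumed baseline-to-week-12 correlation and whether 1.52 is the SD of change or of the score.

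The cost is wording and a less favourable stated power; no extra participants are needed. If the sponsor prefers to retain 90% power on the stated test, 196/0.80 = 245 per group, 490 in total, would have to be enrolled. The Results section reports 47 enrolled by November 2025 and analysis only after data collection, so the correction can still be made before outcome results are known.

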### Combination Medications

Throughout the trial duration, all concomitant medications will undergo comprehensive monitoring. Additional use of TCM formulations with kidney-nourishing and blood-activating properties is strictly prohibited to ensure protocol compliance and minimize confounding effects.

### Statistical Analysis

All statistical analyses will be conducted using the SPSS software (version 25.0; IBM Corp). The primary analysis will follow the intention-to-treat principle. Measurement data that adhere to a normal distribution will be expressed as means and SDs and compared between groups using the independent-sample *t* test. For intragroup comparisons (eg, baseline vs 12-week follow-up), paired *t* tests will be used. Data that do not follow a normal distribution will be expressed as medians and ranges, and the Mann-Whitney *U* test will be used for intergroup comparisons. Count data and categorical variables will be expressed as numbers and percentages and compared using the Pearson chi-square test or Fisher exact test as appropriate.

For the primary outcome analysis, the change in MoCA score from baseline to 12 weeks will be compared between groups using an analysis of covariance adjusting for the baseline MoCA score to enhance precision. A similar analysis of covariance approach will be applied to analyze changes in secondary continuous outcomes (eg, MMSE, VaDAS-cog, and TMT-A and TMT-B scores), with respective baseline scores included as covariates. To explore independent factors associated with cognitive improvement, significant variables identified in univariate analyses will be included in a multivariate linear regression model. All tests will be 2-tailed, and a *P* value of <.05 will be considered statistically significant.

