The underlying mechanisms of cognitive impairment in CSVD remain incompletely elucidated. Neuroimaging modalities, particularly magnetic resonance imaging, have provided critical insights into potential pathophysiological correlates. Current evidence demonstrates associations among lacunar infarcts, white matter hyperintensities, cerebral atrophy, and cognitive deficits [11-13], whereas the presence and burden of cerebral microbleeds exhibit modest yet significant impacts on executive function and information processing speed [14,15]. However, the role of perivascular spaces in cognitive decline remains inconclusive based on extant data [16].

Despite the high prevalence and substantial societal burden of CSVD-related cognitive impairment, targeted therapeutic research remains limited. Current interventions predominantly derive from VaD studies, where cholinesterase inhibitors (eg, donepezil, rivastigmine, and galantamine) are used to enhance synaptic acetylcholine levels and mitigate amyloid β protein generation and deposition, thereby ameliorating cognitive dysfunction [17-21]. While these agents demonstrate modest cognitive benefits, they are associated with clinically significant adverse effects, including severe gastrointestinal disturbances (eg, nausea and vomiting), dizziness, and bradycardia [22,23]. Other pharmacotherapies with putative efficacy in vascular cognitive impairment (VCI), such as *Ginkgo biloba* extracts and nimodipine, require further validation through randomized controlled trials (RCTs) [24,25]. Traditional Chinese medicine (TCM) offers a unique therapeutic paradigm for CSVD. The yin deficiency and blood stasis theory constitute the principal TCM pathogenesis framework, positing dual involvement of the kidney and brain. Guided by this theory, the zishenyizhi decoction (nourishing the kidney and enhancing intelligence decoction) has been empirically used to modulate CSVD progression.

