## Methods

### Study Setting

This multicenter prospective observational nonrandomized controlled study (registered at the International Traditional Medicine Clinical Trial Registry; ITMCTR2025000553) enrolled 246 patients with CSVD-associated cognitive impairment of yin deficiency and blood stasis syndrome from 4 institutions—Hunan Provincial Hospital of Integrated Traditional Chinese and Western Medicine, Yiyang First Hospital of Traditional Chinese Medicine, Liuyang Hospital of Traditional Chinese Medicine, and Shimen County Hospital of Traditional Chinese Medicine. Eligible participants were stratified into 2 groups based on zishenyizhi pill use: the intervention group received guideline-based conventional Western medical therapy combined with zishenyizhi pill for 12 weeks, whereas the control group received guideline-based conventional integrated Chinese-Western therapy. Treatment for all enrolled participants was initiated during the stable phase of their outpatient visit or inpatient stay, immediately following the baseline assessment and confirmation of eligibility. Over the 12-week study period, multidomain cognitive assessments (executive function, attention, and processing speed) were conducted to evaluate the efficacy of zishenyizhi pill in CSVD-related cognitive impairment and explore its underlying mechanisms. The trial workflow is summarized in Figure 1. The evaluations and visits will be conducted according to the testing schedule in Table 2.

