### Interventions

All participants were stratified into 2 groups based on zishenyizhi pill administration: the intervention group and the control group, each comprising 123 patients. Both groups received standardized Western pharmacological therapy, including antihypertensive treatment, antiplatelet therapy, and lipid-lowering therapy. The intervention group additionally received the zishenyizhi pill at a dosage of twice daily for 12 consecutive weeks.

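### The primary comparison of nonrandomised groups adjusts only for baseline MoCA, leaving out the group differences that the protocol itself expects

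*Protocol article*

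**What the plan says.** **Group formation.** Study Setting: "Eligible participants were stratified into 2 groups based on zishenyizhi pill use". Interventions repeats it: "All participants were stratified into 2 groups based on zishenyizhi pill administration". Patients come from 4 hospitals (Study Setting) and from outpatient and inpatient departments (Participants).

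**Treatment estimate.** Under Statistical Analysis, the primary outcome is the MoCA change to week 12, "compared between groups using an analysis of covariance adjusting for the baseline MoCA score to enhance precision". Secondary continuous outcomes follow the same approach, "with respective baseline scores included as covariates".

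**The only multivariable model.** Same section: "To explore independent factors associated with cognitive improvement, significant variables identified in univariate analyses will be included in a multivariate linear regression model".

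**What the authors expect.** Limitations: "The nonrandomized observational design carries an inherent risk of selection bias and confounding", and "baseline differences in patient characteristics—such as disease severity, comorbidities, and socioeconomic status—may persist" between the groups.

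**The concern.** In a randomised trial, baseline adjustment serves mainly to sharpen the estimate, and one strong covariate may be enough. Here nothing balances the groups by design, so adjustment must also remove confounding. The protocol gives precision as its reason for adjusting, and its covariate set fits that reason only.

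The authors name severity, comorbidities and socioeconomic status as plausible imbalances, then specify a primary model with no term for comorbidity or socioeconomic status and with severity represented only through the MoCA score. Centre and care setting are absent too. So is cognitive medication at baseline, although the Introduction says of cholinesterase inhibitors: "While these agents demonstrate modest cognitive benefits".

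At stake is the study's main estimate. The planned difference is small (0.5 points, 0.33 SD), so a moderate imbalance in one prognostic factor could make up a noticeable part of it or cancel a noticeable part of it.

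**Working it through.** **1. Which confounders reach the treatment estimate?**

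| Source of difference | Handled in the plan? |
|---|---|
| Baseline global cognition | Yes, through baseline MoCA |
| Other causes of cognitive impairment, TCM syndrome type, age under 60 | Restricted by the eligibility criteria |
| Recent or added kidney-nourishing or blood-activating herbal medicines | Restricted by Exclusion Criteria and Combination Medications |
| Comorbidity, socioeconomic status, severity beyond MoCA | Named in Limitations; in no treatment model |
| Centre, inpatient or outpatient, age within the range from 60 up | In no treatment model |
| Cognitive medication in use at baseline | Concomitant drugs are monitored; not in the model |

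The multivariable regression does not fill the gap. It looks for predictors of improvement and is not designated as the treatment comparison. Its variables are chosen by univariate significance, a rule that can drop a real confounder and would admit treatment group itself only if that were significant.

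**2. How large could the bias be?** The plan states no figure for this, so there is none to reproduce.

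Inputs from Sample Size: difference 0.5, SD 1.52, 98 evaluable per group, two-sided alpha 0.05. (Whether 98 follows from its stated inputs is a separate matter; it is used here only as the planned evaluable number.)

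Assumed inputs, with no source in the documents: r, the standardised effect of the omitted confounder on MoCA change given baseline MoCA; and d, its imbalance between groups in SD.

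- Standard error = 1.52 × √(2/98) = 1.52 × 0.1429 = 0.217.
- Bias = r × d × 1.52.
- Rejection rate with no true effect = Φ(−1.96 − bias/SE) + 1 − Φ(1.96 − bias/SE).

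| r | d | Bias (points) | Share of 0.5 | Bias/SE | False-positive rate |
|---|---|---|---|---|---|
| 0.1 | 0.2 | 0.03 | 6% | 0.14 | 5.2% |
| 0.2 | 0.5 | 0.15 | 30% | 0.70 | 10.8% |
| 0.3 | 0.3 | 0.14 | 27% | 0.63 | 9.7% |
| 0.3 | 0.5 | 0.23 | 46% | 1.05 | 18.3% |

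The sign is unknown. With the last row's bias reversed, a true benefit of 0.5 would be estimated on average at 0.50 − 0.23 = 0.27. Several omitted confounders could add up or partly cancel.

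**3. What does adjustment cost?** If the added covariates explain a share R² of treatment choice, the standard error is multiplied by 1/√(1 − R²): 1/√0.90 = 1.05 and 1/√0.80 = 1.12. If they also explain outcome variance, the factor is √[(1 − R²outcome)/(1 − R²treatment)], which is 1.00 when both are 0.10. These R² values are assumed.

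**The case against.** The strongest reply is that the authors disclose the problem: Limitations says that internal validity is compromised and causal inference constrained, and the later sections leave definitive efficacy to a randomised trial. That candour stands. But disclosure suits confounders that cannot be measured; it does not justify omitting those that the authors can name and could record.

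A second reply is that a full covariate list belongs in an analysis plan not shown here. That would answer silence. The article instead states the primary model, its covariate and the reason for it, so an analysis plan with a different primary model would contradict it.

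Several stronger readings are tempting and not supported:

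- A reader might infer that patients choose their own group. The text says that groups follow pill use, not who decides.
- A reader might infer that all confounding passes into the estimate. Baseline MoCA, the eligibility restrictions, the herbal washout and the ban on certain added TCM remove part of it.
- A reader might conclude that the 5% error rate certainly fails. Every input to the bias figures is assumed, and at the weak end the rate barely moves.
- A reader might take Limitations to claim that grouping by pill use is a safeguard. It calls the grouping a stratification in spite of which differences may remain: loose wording, not such a claim.
- A reader might suppose that cholinesterase inhibitor use differs between groups. Nothing shows this, and the background therapies listed under Interventions are examples, not a closed list.
- A reader might assume that the needed covariates are already on file. Table 2 lists only general information and medical history, without fields.

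**Conclusion.** The point holds. Followed as written, the analysis gives a primary treatment estimate that is unadjusted for centre, care setting, age, education, comorbidity and baseline cognitive medication, in a nonrandomised comparison whose authors expect imbalances of this kind. The fault is in a stated rule, not in missing detail, and the secondary outcomes share it.

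The size is conditional: for one omitted confounder, roughly 6% to 46% of the target difference and a false-positive rate of 5.2% to 18.3% over the assumed range. The direction is unknown. The case for change rests on the design and the stated model, not on any one of these figures.

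**What to change.** **Primary model.** Specify an ANCOVA of MoCA on group, baseline MoCA, centre (where both groups occur within centres) and a fixed list of confounders chosen on subject-matter grounds and measured at baseline only: age, sex, education or another socioeconomic marker, inpatient or outpatient, vascular comorbidities, disease severity, baseline TCM syndrome score, and cognitive medication in use at baseline. Drugs started after baseline should not be on the list. Do not select confounders by univariate P values.

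**Supporting analyses.** Use the same confounder set for the secondary outcomes, each with its own baseline score. Report standardised mean differences between groups. Keep the baseline-only ANCOVA as a sensitivity analysis; propensity-score overlap weighting and an E-value are optional additions.

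**Data.** Confirm that the case report form records each field and add any that are missing now. Results reports 47 of 246 enrolled as of November 2025, so 199 remain; for those already enrolled, a missing field would have to be recovered where possible.

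**Wording.** Stop describing grouping by pill use as stratification in Limitations, and likewise in Study Setting and Interventions.

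**Cost.** A protocol amendment, possibly a few added fields, and a standard error about 5% to 12% larger if the covariates explain 10% to 20% of treatment choice, before any gain from explained outcome variance. Unmeasured confounding remains, and the report should say so.

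### The exploratory regression screens variables by univariate significance and does not say that treatment or baseline MoCA stays in, although it is the only described model that could adjust for other confounders

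*Protocol article*

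**What the plan says.** All of this stands in the protocol article.

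- **Primary analysis (Statistical Analysis).** The 12-week change in MoCA is "compared between groups using an analysis of covariance adjusting for the baseline MoCA score to enhance precision". Secondary continuous outcomes are handled in the same way, each with its own baseline score.
- **Exploratory regression (Statistical Analysis).** The purpose is given as "To explore independent factors associated with cognitive improvement", and the rule is that "significant variables identified in univariate analyses will be included in a multivariate linear regression model". The section gives no candidate list, no threshold specific to the screen and no variable that is retained regardless of its P value.
- **Significance level (Statistical Analysis).** The general rule is "All tests will be 2-tailed, and a *P* value of <.05 will be considered statistically significant". As no other threshold is given, I take .05 as the screening threshold.
- **Design (Study Setting, Interventions, Limitations).** Groups are formed by pill use, without randomization. The Limitations section accepts that differences in disease severity, comorbidities and socioeconomic status may remain between the groups and affect interpretation.

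**The concern.** The primary and secondary ANCOVAs adjust for one variable, the baseline score. The regression is the only other model described, so it is the only place where severity, comorbidity or centre could enter alongside treatment. A reader who wants to know whether a difference between groups survives adjustment has no other described analysis to consult.

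A univariate outcome screen is a weak tool for that purpose, for three reasons.

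1. It judges each variable by its crude association with the outcome, which is the quantity that confounding distorts. A confounder with a modest crude association can be dropped.
2. If treatment is itself a candidate, a benefit that is hidden because sicker patients received the pill can fail the screen and then never be adjusted.
3. The surviving coefficients are tested in the data that selected them, as if the model had been fixed beforehand. Their estimates, P values and intervals ignore the selection.

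**Working it through.** **Inputs.** From Sample Size: "we assumed a mean difference (δ) in MoCA score change of 0.5 between the 2 groups", "with a common SD (σ) of 1.52", "With a significance level (α; 2-sided) set at .05", a claimed power of 90%, 1:1 allocation, 98 evaluable and 123 enrolled per group. From Statistical Analysis: two-tailed .05. The number of candidate variables is not given, so it is assumed where needed.

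**1. The plan's own sample size.** n per group = 2(1.960 + 1.282)² × 1.52² / 0.5² = 194.2, rounded up to 195. The stated 98 is not reproduced. Without the factor 2 the formula gives 97.1, rounded up to 98. The dropout step does reproduce: 98 / 0.8 = 122.5, rounded up to 123. The sample size is a separate point. It matters here because it sets the power of any screen on treatment.

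**2. Chance that treatment fails the screen, if it is a candidate and there is no confounding.** This is 1 minus the power of a two-sample t test (noncentral t), with SE = 1.52 × √(2/n) and noncentrality 0.5/SE.

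| n per group | SE | 0.5/SE | Fails P<.05 |
|---|---|---|---|
| 98 | 0.217 | 2.30 | 37% |
| 123 | 0.194 | 2.58 | 27% |
| 195 (claimed 90% power) | 0.154 | 3.25 | 10% |

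As an illustration under my own assumption, suppose confounding reduced the crude difference from 0.5 to 0.35. Failure would then be about 64% at 98 per group and 56% at 123.

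**3. Inflation when treatment is retained.** Given that the estimate passed the screen, its mean is approximately δ + SE × φ(a)/Φ(a), with a = δ/SE − t(.975).

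- 98 per group: a = 2.303 − 1.972 = 0.330, so 0.5 + 0.217 × 0.378/0.629 = 0.63.
- 123 per group: a = 2.580 − 1.970 = 0.610, so 0.5 + 0.194 × 0.331/0.729 = 0.59.

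Simulation of the full two-step procedure (4,000 runs per setting) agrees: 0.62 to 0.63 and 0.58 to 0.59, against a true 0.5.

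**4. P values after screening.** In the same simulations, a variable with no true effect that passed the screen stayed significant in the final model in about 80% to 87% of cases. A final-model P<.05 is therefore not a 5% test for a variable chosen this way.

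**5. Does screening create extra false factors?** Share of runs with at least one false factor in the final model, 98 per group, independent null candidates (number assumed):

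| Null candidates | Screened model | Full model, no screen |
|---|---|---|
| 5 | 20% | 22% |
| 10 | 35% | 39% |
| 20 | 59% | 63% |

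Screening is no worse than the full model. With 10 null candidates imbalanced by 0.3 to 0.5 SD between the groups (assumed), the figures are 30% to 33% screened and 39% full. The excess over 5% comes from testing many variables without correction.

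**The case against.** The strongest reply is that the treatment effect is tested elsewhere. The primary ANCOVA compares the groups and always contains treatment, and the regression is introduced as exploration. This stands. A reader might infer that the rule can remove the study's treatment effect; the text does not support that, because no screen applies to the primary or secondary ANCOVAs.

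Second, the text does not say whether treatment is a screened candidate or a fixed term. This also stands. The failure rates above are conditional on treatment being screened; they describe what the wording leaves open and are not a stated rule.

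Third, a reader might infer that screening manufactures false independent factors and point to the 40% to 64% chance that at least one of 10 to 20 null candidates passes (1 − 0.95^10 and 1 − 0.95^20). That is ordinary multiplicity over an assumed number of candidates. Step 5 shows that a full model tested at the same level does no better, so the figure does not measure harm from this rule.

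Fourth, the 37% is high largely because 98 per group falls short of the 195 that the stated inputs require; at the claimed power it is 10%. This is right, and is why all three figures are given.

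Finally, candidate lists may be left to an analysis plan that is not shown. That would answer a complaint about missing detail. It does not answer this one, because entry by univariate significance is a stated rule, and an analysis plan with a fixed model would be replacing it.

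**Conclusion.** The point holds in a limited form. The plan fixes an outcome-driven screen for the only described model that could adjust for more than the baseline score, in a comparison it admits may be confounded, and it protects neither treatment nor baseline MoCA.

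If treatment is screened at P<.05 and the difference is 0.5 with SD 1.52 and no confounding, it would be dropped in about 37% of studies at 98 per group, 27% at 123 and 10% at 195. When retained at 98 per group it would be overestimated by about a quarter (0.63/0.5 = 1.26). Inference after screening is not valid at its nominal level.

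The primary test is not affected, and screening as such does not raise the rate of false factors above that of a full model. As the model is exploratory, this is a cheap improvement and not a threat to the primary result.

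**What to change.** Replace the univariate screen with a prespecified linear model. Keep treatment, baseline MoCA and centre in it regardless of significance, and add a pre-listed set of clinically chosen baseline variables from the general information and medical history already collected at week 0. Report every coefficient with its 95% CI, and describe the predictor findings as exploratory and not corrected for multiplicity. The fixed model cures the possible loss of treatment and the selection bias in estimates, P values and intervals. It does not lower the chance of a false factor, which is why the multiplicity statement is needed.

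The cost is a sentence or two in the analysis plan, a few degrees of freedom and a less sparse model. With 2 × 98 = 196 evaluable patients, 10 to 15 covariates are affordable. No data collection changes. The Results section reports 47 of the planned 246 participants enrolled by November 2025, with analysis to start only after data collection ends, so the list can still be fixed credibly in advance.
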